### Diagnosis of ATE

Prior to algorithm development, data will be divided into training and validation sets, with a model being derived using the training data. The training phase will include examination of potentially confounding and interacting variables (e.g., age, sex, time from injury until blood draw). Any confounding variables will be included as covariates in the model. Variables with insignificant interaction, as determined by backward selection, will be omitted. The model will provide a probability/score that a subject has ATE. The c-statistic will be reported, and a threshold selected to ensure the model meets the minimum sensitivity and specificity of 85 and 75%, respectively, with confidence intervals, positive predictive value and negative predictive value reported. Accuracy will be reported as the percentage of all suspected TBI subjects correctly classified as “ATE,” vs. “no ATE,” using the identified threshold. Validation data will be derived in an independent subject set (validation cohort), against which the developed model will be tested for generalizability. *P*-values comparing the AUC, sensitivity, specificity, and accuracy will be reported, with alpha defined as < 0.05. Sample size calculation was performed in PASS statistical software (32) using an assumed prevalence of 50% ATE in the subjects enrolled with blunt head injury. The final number of evaluable subjects for the “ATE,” and “no ATE” cohorts, should each not exceed 240, which makes the total number of evaluable subjects 480. An equal number of subjects are needed for algorithm validation (*n* = 480).

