### Prognosis of ATE

A separate model will be fit for symptoms at each post-enrollment time point, with data evaluated during the modeling phase, to determine the prognostic output report. Results will be grouped into low and high risk. Based on the data from the modeling/training phase, the symptom categories that are statistically supported, with sufficient prevalence to make a justified prognostic claim, will be reported. If applicable, symptoms categories may be combined into one overarching composite result, and defined as either low or high risk. Data handling for modeling will be the same as the diagnostic analysis, with the models identifying the likelihood that a subject will experience ATE symptoms at 14, 30, and 90 days.

Sample size for TBI subjects adjudicated as high or low risk for ATE symptoms at 14, 30 and 90-days post-injury is based on estimated prevalence of 60% of subjects having unresolved or emergent injury-related symptoms in the suspected ATE population at each time point (30). Using published and internal information on prevalence, as well as predefined sensitivity, specificity, confidence intervals, error, the total number of ATE subjects needed was calculated. The number of subjects with high risk of outcomes needed, the target condition for the prognosis, will be 236 evaluable subjects. The number of subjects without ATE will be 157, yielding a total number of subjects of 393 for algorithm training. With the estimated prevalence of ATE being 50%, a total of 786 blunt head trauma subjects is needed for algorithm training. This study design uses the same sample sizes for both training and validation phases, just as in the diagnostic models. Therefore, the same number of blunt head trauma subjects (*n* = 786) are needed for validation. To provide sufficient data for prognosis modeling in training and validation cohorts, up to 1,600 suspected ATE subjects will be needed. Enrollment numbers are subject to increase or decrease pending on true prevalence, results of data analysis and/or attrition.

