The data collected in the clinical study that is directly related to study endpoints follows a BRAINBox Solutions blinding plan. Subjects from the training phase of the ATE diagnosis cohort may also be used in the training phase of the prognostic evaluation. Subjects from the validation phase of the ATE diagnosis cohort may be used in the validation phase of the prognostic evaluation. Therefore, the total number of suspected ATE patients should not exceed 1,600. In the event the actual prevalence differs from the assumed prevalence, the study design will include 2,000 blunt head trauma subjects as a maximum enrollment number.

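### The ceiling of 240 evaluable subjects per diagnostic class, followed literally, would tie PPV and NPV to about 50% prevalence, and it conflicts with the stated denominator for accuracy

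*Protocol article*

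**What the plan says.** All references are to the protocol article.

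- **Diagnosis of ATE, reporting.** A threshold is chosen to meet the minimum sensitivity and specificity, "with confidence intervals, positive predictive value and negative predictive value reported". No analysis set or prevalence basis is given for the two predictive values.
- **Diagnosis of ATE, accuracy.** "Accuracy will be reported as the percentage of all suspected TBI subjects correctly classified".
- **Diagnosis of ATE, size.** The calculation was made "using an assumed prevalence of 50% ATE in the subjects enrolled with blunt head injury". The limit is then stated: "The final number of evaluable subjects for the “ATE,” and “no ATE” cohorts, should each not exceed 240". The total is given as 480. For the second phase, "An equal number of subjects are needed for algorithm validation", again 480.
- **Prognosis of ATE, size.** Here "a total of 786 blunt head trauma subjects is needed for algorithm training", and the same number for validation. Diagnostic subjects may be reused in the matching prognostic phase. Enrolment may rise or fall with the true prevalence.
- **Prognosis of ATE, maximum.** The section closes with: "In the event the actual prevalence differs from the assumed prevalence, the study design will include 2,000 blunt head trauma subjects as a maximum enrollment".

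**The concern.** A sample-size calculation normally yields a minimum. This sentence sets a maximum, and sets it separately for each outcome class of the final evaluable set. The total of 480 is reached only when both classes hold 240. More subjects than that are to be enrolled in each phase, so keeping to the ceiling means choosing who is analysed according to the adjudicated diagnosis.

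Sensitivity and specificity are calculated within a class, so such selection leaves them intact. PPV and NPV mix the two classes and depend on the class ratio. Calculated on a set balanced by outcome, they describe a population with 50% ATE, whatever the share among patients who actually present. They are the figures that tell an emergency physician what a positive or negative result means. Intervals calculated on the balanced set would be centred on the wrong value and would not show the problem.

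**Working it through.** **Inputs.** Sensitivity 0.85 and specificity 0.75 (Sample Size Estimation). Ceiling of 240 per class, 480 per phase, assumed prevalence 50% (Diagnosis of ATE). 786 subjects per phase, maximum 2,000 (Prognosis of ATE). The true prevalence *p* is not in the document; 30% to 70% is an assumed range.

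**1. The plan's own totals.** 240 / 0.50 = 480. For prognosis, 236 + 157 = 393 and 393 / 0.50 = 786; two phases make 1,572, within the 1,600 planned. These totals are consistent. The 240 is taken as given; whether it gives enough power is a separate question on which nothing below depends.

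**2. Does the ceiling bind?** At 50% prevalence, 786 subjects give 786 × 0.50 = 393 per class, well above 240. The smaller class is expected to reach 240 when its share is at least 240 / 786 = 30.5%. Both classes therefore fill for *p* from about 31% to 69%, if all 786 are eligible for the diagnostic analysis. If the 2,000 maximum were split equally (an assumption), the limit is 240 / 1,000 = 24%, so both fill from 24% to 76%.

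**3. PPV and NPV on a 240/240 set.**

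- True positives 0.85 × 240 = 204; false negatives 36.
- True negatives 0.75 × 240 = 180; false positives 60.
- PPV = 204 / 264 = 77.3%. NPV = 180 / 216 = 83.3%.

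**4. Values in the enrolled population.**

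- PPV = 0.85*p* / [0.85*p* + 0.25(1 − *p*)]
- NPV = 0.75(1 − *p*) / [0.75(1 − *p*) + 0.15*p*]
- Accuracy = 0.85*p* + 0.75(1 − *p*)

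| Assumed *p* | PPV | NPV | Accuracy | Capped minus enrolled: PPV | NPV |
|---|---|---|---|---|---|
| 30% | 0.255/0.430 = 59.3% | 0.525/0.570 = 92.1% | 78.0% | +18.0 | −8.8 |
| 40% | 0.340/0.490 = 69.4% | 0.450/0.510 = 88.2% | 79.0% | +7.9 | −4.9 |
| 50% | 0.425/0.550 = 77.3% | 0.375/0.450 = 83.3% | 80.0% | 0 | 0 |
| 60% | 0.510/0.610 = 83.6% | 0.300/0.390 = 76.9% | 81.0% | −6.3 | +6.4 |
| 70% | 0.595/0.670 = 88.8% | 0.225/0.330 = 68.2% | 82.0% | −11.5 | +15.2 |

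Differences are in percentage points. At exactly 30% with 786 subjects, 236 ATE subjects are expected (786 × 0.30), so the capped set is 236/240, or 49.6% ATE. The 30% row is therefore almost unchanged, and the 70% row likewise by symmetry.

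**5. Size against sampling error.** In simulation of the capped set, the standard deviation of PPV and of NPV was about 2.0 to 2.2 points. A 95% interval then reaches about 1.96 × 2.0 = 3.9 to 1.96 × 2.2 = 4.3 points either side. The errors at 40% and 60% (4.9 to 7.9 points) already exceed that.

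**6. When only one class fills.** Suppose 480 are enrolled at *p* = 60%. There are 288 ATE subjects, cut to 240, and 192 without ATE, so the set is 240 / 432 = 55.6% ATE. PPV = 204 / (204 + 48) = 81.0% against 83.6%, and NPV = 144 / (144 + 36) = 80.0% against 76.9%. The distortion is partial.

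**The case against.** The strongest reply is that the ceiling is sizing language and not an analysis rule. It directly follows the software calculation at an assumed prevalence, and the next sentence speaks of the number needed for validation. The article uses similar wording loosely elsewhere: a limit of 1,600 suspected ATE subjects is followed at once by a maximum of 2,000. Nothing describes how surplus subjects would be dropped, or says that PPV and NPV come only from the 480. Adjudication follows completion of follow-up, so a class limit could not work at enrolment. PPV and NPV carry no hypothesis test, and a condensed article may leave their analysis set to the SAP.

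Much of this stands, and it rules out two stronger readings. A reader might infer that the plan fixes prevalence at 50%, so that PPV and NPV are wrong whenever the true prevalence differs. The document does not support that: a maximum is not a quota, a 50/50 set arises only if both classes fill and the surplus is removed, and reuse of diagnostic subjects for prognosis is permitted without any statement that all 786 enter the diagnostic analysis. A reader might also infer that accuracy is biased. Its stated denominator is uncapped, and prevalence moves it by only 2 points from 80.0% across 30% to 70%.

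The reply does not dispose of what is written. The sentence limits the final number of evaluable subjects by class, calls 480 their total, and sits in the section that requires PPV and NPV without naming another set. The issue is a stated limit, not silence. With 786 subjects per phase, a limit of 480 evaluable and a denominator of all suspected subjects cannot describe the same set.

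**Conclusion.** The point holds in conditional form. If the ceiling is applied as written and no re-weighting is done, PPV and NPV would describe about 50% prevalence and not the enrolled population. The errors are about 5 to 8 points at 40% or 60% prevalence and about 9 to 18 points at 30% or 70%; they vanish at 50%. This rests on sensitivity 0.85 and specificity 0.75, on the assumed prevalence range, and on all 786 subjects per phase being eligible. If fewer are eligible and only one class fills, the distortion is smaller.

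Sensitivity and specificity, the measures on which the study is sized, are not affected. For accuracy the finding is a contradiction to reconcile, not a demonstrated bias. The change should be made because the plan itself anticipates a prevalence other than 50%.

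**What to change.** State under Diagnosis of ATE that 240 per class is a sizing target (a minimum) and does not limit the analysis set. Calculate PPV, NPV and accuracy on all adjudicated suspected ATE subjects in the phase. This also removes the conflict with the definition of accuracy.

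If a capped set is kept for the sensitivity and specificity tests, derive PPV and NPV from those estimates by Bayes' rule, using the prevalence observed among all adjudicated suspected ATE subjects. The intervals should include the uncertainty in that prevalence. Under either option, report the prevalence beside each figure.

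The cost is about one sentence of analysis wording. The subjects are already to be enrolled and adjudicated for the prognostic analysis, so no further patients or procedures are needed. The downside is that the reported PPV or NPV may be less favourable.

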### Prognosis of ATE

A separate model will be fit for symptoms at each post-enrollment time point, with data evaluated during the modeling phase, to determine the prognostic output report. Results will be grouped into low and high risk. Based on the data from the modeling/training phase, the symptom categories that are statistically supported, with sufficient prevalence to make a justified prognostic claim, will be reported. If applicable, symptoms categories may be combined into one overarching composite result, and defined as either low or high risk. Data handling for modeling will be the same as the diagnostic analysis, with the models identifying the likelihood that a subject will experience ATE symptoms at 14, 30, and 90 days.

Sample size for TBI subjects adjudicated as high or low risk for ATE symptoms at 14, 30 and 90-days post-injury is based on estimated prevalence of 60% of subjects having unresolved or emergent injury-related symptoms in the suspected ATE population at each time point (30). Using published and internal information on prevalence, as well as predefined sensitivity, specificity, confidence intervals, error, the total number of ATE subjects needed was calculated. The number of subjects with high risk of outcomes needed, the target condition for the prognosis, will be 236 evaluable subjects. The number of subjects without ATE will be 157, yielding a total number of subjects of 393 for algorithm training. With the estimated prevalence of ATE being 50%, a total of 786 blunt head trauma subjects is needed for algorithm training. This study design uses the same sample sizes for both training and validation phases, just as in the diagnostic models. Therefore, the same number of blunt head trauma subjects (*n* = 786) are needed for validation. To provide sufficient data for prognosis modeling in training and validation cohorts, up to 1,600 suspected ATE subjects will be needed. Enrollment numbers are subject to increase or decrease pending on true prevalence, results of data analysis and/or attrition.

The data collected in the clinical study that is directly related to study endpoints follows a BRAINBox Solutions blinding plan. Subjects from the training phase of the ATE diagnosis cohort may also be used in the training phase of the prognostic evaluation. Subjects from the validation phase of the ATE diagnosis cohort may be used in the validation phase of the prognostic evaluation. Therefore, the total number of suspected ATE patients should not exceed 1,600. In the event the actual prevalence differs from the assumed prevalence, the study design will include 2,000 blunt head trauma subjects as a maximum enrollment number.

## Conclusions

This protocol proposes to collect data using a multi-modality approach, including blood biomarkers, clinical characteristics, neurocognitive and neuropsychological assessments, to develop diagnostic and prognostic algorithms for ATE. The validation phase will determine the accuracy of the BRAINBox ATE Test as an aid to the diagnosis of ATE, and as an objective determination of a patient's risk to develop post-concussive symptoms.

## Ethics Statement

The studies involving human participants were reviewed and approved by the Local Ethics Committee of each participating institution. The patients/participants provided their written informed consent to participate in this study.

